**Figure 1 F1:**
[figure not shown]
Test flow chart.

Potential participants will be invited to an initial assessment (first visit) consisting of an inclusion and exclusion criteria screening. If eligible, participants will be asked for informed consent and will undergo assessment of Psoriasis area severity index (PASI), dermatology life quality index (DQOLS), and score of Pruritus Degree by PGA, lesion photos and vital signs, full blood count, kidney and liver function blood tests, electrocardiogram, stool examination and urine (routine chemical examinations).

A total of 72 patients with recurrent PV will be randomized (in a 1:1 ratio) to receive oral Chinese herbal medicine JWLXXF or oral acitretin for 8 weeks. During the observation phase, psoriasis symptom measures will be self-reported by participants and recorded in a daily or weekly diary. Face-to-face assessments with blinded assessors will be scheduled at weeks 2, 4, 6, and 8 (Fifth visit), with further data collected, including assessment of PASI, DQOLS, and score of Pruritus degree by PGA, lesion photos, drug adherence, vital signs, adverse events and cause analysis of shedding (Table 1). The conversation will be made to 72 patients, at the time of medical treatment, to check adherence to the dosage guidelines and to monitor adverse events. Routine chemical examinations, laboratory assessments of efficacy and safety evaluation will also be scheduled at the end of the 8-week period.

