### Sample size calculation

3.8

Due to the unknown potential primary outcome at this stage, the sample size was calculated by reference to a standardized effect size. An effect size of 0.9 SD was chosen with consideration of the drug cost and patients’ motivation to adhere to the treatment. To detect a difference of 0.9 SD with 90% power using a 5% significance level, a sample size of 30 per arm would be required. Considering 20% dropout rate, the total sample size should be adjusted to 36 for each group.

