### Statistical analysis

3.10

SPSS Statistics 17.0 (IBM SPSS Inc., Armonk, NY) will be used for the statistical analysis of data, which will be carried out by independent statisticians. The Chi-square test will be used to evaluate the basic baseline characteristics and primary outcomes of the 2 groups. The Spearman rank correlation analysis of the correlation between PASI and biochemical indexes, will be used. The secondary outcomes will be evaluated by means, standard deviations and medians. The one way ANOVA test will be used to compare the mean of multiple samples, the LSD test for the homogeneous variance, and the Tamhane T2 test for the uneven variance. *P* < .05 will be considered as statistically significant.

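### PASI is read at baseline and at four treatment visits, but the named tests use neither the repeated readings nor baseline as a covariate, and the elimination criteria make a completer comparison likely

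*Protocol article*

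**What the plan says.** All references are to the protocol article.

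- **Outcome.** Section 3.5.1 lists PASI first among the primary outcomes.
- **Visits.** Section 2 has PASI assessed at the initial visit. It then states: "Face-to-face assessments with blinded assessors will be scheduled at weeks 2, 4, 6, and 8 (Fifth visit"), with PASI among the items collected.
- **Tests.** Section 3.10 gives the chi-square test for baseline characteristics and primary outcomes of the two groups. For means it says "The one way ANOVA test will be used to compare the mean of multiple samples", followed by LSD or Tamhane T2 comparisons. Spearman correlation is reserved for PASI against the laboratory indices. No repeated-measures or covariate-adjusted method is named.
- **Dropout.** Section 3.8 says "a sample size of 30 per arm would be required" and then "Considering 20% dropout rate, the total sample size should be adjusted to 36 for each group". It does not say whether the 20% is lost by week 8 or over the whole trial, which includes a 52-week follow-up.
- **Elimination.** Section 3.1.3 eliminates patients who cannot take the medication or attend review as required, whose records are incomplete, who stop treatment themselves, or who have a major negative event during the trial. These can all happen after randomisation.

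**The concern.** Enrolling 36 instead of 30 per arm restores numbers. It does not undo selection if those who leave differ from those who stay. A patient who leaves after week 4 or week 6 already has two or three PASI readings after baseline, and these carry information about the missing week-8 value. A single-time-point comparison makes no use of them.

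Departure could plausibly differ by arm. The arms take different drugs (section 3.2), and section 3.7 advises patients with adverse events or abnormal liver or kidney results to stop trial medication. If the elimination criteria then remove these patients, the week-8 comparison is made in a selected group.

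A second primary outcome is touched as well. Week-8 PASI improvement decides who enters follow-up, and so sets the denominator of the recurrence rate. At stake are some bias and some unused precision in the PASI comparison.

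**Working it through.** **1. The plan's own figure.** Inputs from section 3.8: 0.9 SD, 90% power, 5% level (taken as two-sided, since sidedness is not stated). Section 2 gives 1:1 allocation.

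- Normal formula: n = 2(1.960 + 1.282)² / 0.9² = 25.9, so 26 per arm. The exact t-test gives 27. The stated 30 is somewhat conservative.
- Allowance: 30 × 1.20 = 36, the stated figure. (Dividing by 0.8 would give 37.5, so 38; this does not affect the present point.)

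**2. Power if only completers count and all 20% leave before week 8.** 36 × 0.8 = 28.8 per arm. Non-centrality = 0.9 × √(28.8/2) = 3.42. The two-sided t-test has 91.9% power, above the planned 90%.

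**3. What the earlier visits add to power (assumed correlations).** If all dropouts leave after week 6 and the visit correlation is AR(1) with ρ = 0.7, the variance of an arm's week-8 mean (SD = 1) under a likelihood analysis is

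(1 − ρ²)/28.8 + ρ²/36 = 0.51/28.8 + 0.49/36 = 0.0313,

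an effective n of 31.9 per arm against 28.8. Over ρ = 0.5 to 0.9, AR(1) or compound symmetry, with dropout spread evenly or all after week 6, effective n runs from 29.4 to 34.9 and power from 92.3% to 95.9%. The gain over 91.9% is 0.4 to 4.0 percentage points.

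**4. Bias.** A hand check first: if the 20% who leave one arm are 0.5 SD worse than its completers (assumed), that arm's completer mean is off by 0.2 × 0.5 = 0.1 SD.

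Two simulations of 3,000 runs used 36 per arm, a correlation of 0.65 between adjacent visits and 0.42 from baseline to week 8, and dropout driven by the observed change at the last visit. All of these inputs are assumed. The first had 18 to 28% dropout; in the null case of the second, about 19 to 24% per arm were lost.

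| Situation | Raw week-8 PASI, completers | Baseline-adjusted, completers | Change from baseline, completers | Repeated-measures likelihood |
|---|---|---|---|---|
| True 0.90 SD, first simulation | 0.86–0.88 | 0.78–0.85 | not run | 0.90 |
| True 0.90 SD, second simulation, same dropout rule in both arms | 0.88–0.89 | 0.85–0.87 | 0.81–0.86 | 0.90–0.91 |
| True 0.90 SD, response-driven dropout in control arm only | not reported | not reported | 0.69 | 0.90 |
| No effect, response-driven dropout in one arm only (size of bias) | 0.04–0.07 | 0.08–0.13 | 0.14–0.22 | within 0.01 of 0 |

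For raw week-8 PASI with a true effect, the first simulation gives a bias of 0.90 − 0.88 = 0.02 to 0.90 − 0.86 = 0.04 SD. The second gives 0.01 to 0.02.

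**5. Precision.** For unadjusted completers, SE = √(2/n). With 18% lost, n = 29.5 and SE = 0.260; with 28% lost, n = 25.9 and SE = 0.278. The simulated value was about 0.27, falling to about 0.24 with the repeated-measures analysis. Baseline adjustment alone multiplies the SE by √(1 − 0.42²) = 0.908, and 0.27 × 0.908 = 0.245. Most of the fall therefore comes from using baseline PASI, and the rest from the intermediate visits.

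**The case against.** - **The article does not state a completer analysis.** A reader might infer from the dropout allowance and the named tests that dropouts' earlier PASI values are thrown away. Nothing says this. The article gives no analysis set and no rule for missing values, and both may sit in an analysis plan that is not shown. The elimination criteria speak of exclusion from participation, not from analysis. This stands. A completer comparison is the likely reading, not a stated one.
- **The sample-size sentence is not at fault here.** It sets a number, does not place the 20% before week 8, and leaves adequate power. Some loss may fall in follow-up, after all treatment-phase PASI readings are complete. This stands.
- **One-value tests can keep dropouts.** Chi-square on PASI75 can include every randomised patient if absences count as non-response, and that percentage improvement already uses baseline through its definition. This stands, and the fix retains it.
- **The ANOVA may not be meant for the two-arm comparison.** LSD and Tamhane T2 suit three or more groups, and the trial also has healthy and recovered groups. This is plausible. It leaves chi-square as the only test clearly assigned to PASI between arms, which still does not use the series of readings.
- **The larger bias figures belong to other analyses.** The roughly 0.12 SD null bias is for baseline-adjusted completers, which the protocol does not name. The simulations also let dropout depend on observed PASI, the condition that favours the likelihood analysis; departures for side effects unrelated to PASI were not simulated. This stands.

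The choice of tests is nevertheless stated, and it leaves scheduled PASI readings unused.

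**Conclusion.** The point holds as an improvement to the stated analysis, not as a demonstrated large bias or a wrong sample size. The named tests use neither the repeated PASI readings nor baseline PASI as a covariate, and the elimination criteria make a completer comparison likely unless something outside the article prevents it.

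Planned power is not endangered: about 92% with 28.8 completers per arm. Under the assumed correlations and dropout rule, bias in raw week-8 PASI is about 0.02 to 0.04 SD when the true effect is 0.9 SD. It is larger for change from baseline, or where response-related dropout differs between arms. The SE would fall from about 0.27 to 0.24 SD, mostly through baseline adjustment.

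A reader might go further and conclude that the plan discards dropouts' data or that its PASI result will be materially biased. The article supports neither conclusion: it fixes no missing-data rule, and the size of any bias depends on correlations and dropout patterns it does not give.

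**What to change.** In section 3.10:

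1. Analyse PASI by a mixed model for repeated measures in all randomised patients with at least one post-baseline PASI. Include arm, visit, arm-by-visit and baseline PASI, and take the week-8 contrast between arms as the result.
2. Keep the chi-square test for week-8 PASI75, counting randomised patients without a week-8 value as non-responders.
3. State that meeting an elimination criterion in section 3.1.3 does not remove a randomised patient from either analysis.

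The cost is analysis wording and slightly more programming, with no new visits or patients. The downside is that the model assumes dropout depends on observed PASI. Departures driven by something unrecorded could still bias the result.

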### Data management and quality control

3.9

In this study, the data will be collected from participants through face-to-face assessment and recorded in the case report form. The original recorded data in the case report form cannot be changed at will. If it is necessary to make corrections, it shall use the correct writing format with the signature and time on the name of the person who made the change. At the end of each evaluation, all data will be added into the database by the people who did not know the task of the team nor did participate in the case collection. The researchers who will participate in the experiment will receive advance training and education, to ensure a high experimental quality. The experimental supervision will be commissioned by the Sichuan provincial Chinese medicine clinical trial organization.

### Statistical analysis

3.10

SPSS Statistics 17.0 (IBM SPSS Inc., Armonk, NY) will be used for the statistical analysis of data, which will be carried out by independent statisticians. The Chi-square test will be used to evaluate the basic baseline characteristics and primary outcomes of the 2 groups. The Spearman rank correlation analysis of the correlation between PASI and biochemical indexes, will be used. The secondary outcomes will be evaluated by means, standard deviations and medians. The one way ANOVA test will be used to compare the mean of multiple samples, the LSD test for the homogeneous variance, and the Tamhane T2 test for the uneven variance. *P* < .05 will be considered as statistically significant.

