#### Primary outcomes

3.5.1

(1)PASI: assess the severity of the disease.(2)Laboratory assessments: the number and distribution of Th1, Th2, Th17, Treg, Th22, and Th9 cells will be determined by ELISA. The expression of the transcription factors T-bet, GATA3, ROR gamma t, Foxp3 gene will be investigated by PCR and WB. The screening of cytokines, such as IFN-gamma, IL-4, IL-17A, IL-17F, IL-22, TGF-beta, IL-10 and IL-9 will be performed by Bio-Plex suspension chip.(3)Recurrence rate = recurrence cases/follow-up cases ∗100%

Note:

No recurrence criteria: the same as the end of treatment and lesion limitation. Recurrence criteria: new skin lesions appearing in the patients who were clinically cured or have the original skin lesions expanding, the color turning red, the scale increasing and the PASI score increasing for ≥ 1.

(1) Mitigation period: this remission period - the last remission period.

Note:

The last remission period: the time from the last clinical cure to the recurrence. This remission: the time interval from the end of JWLXXF treatment to the next recurrence.

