### Clinical efficacy evaluation basis

4.2

For moderate and severe psoriasis, PASI score is still the “gold standard” to evaluate the severity of psoriasis.^[29]^ According to the research, patients with sustained and efficient response to PASI score have a better quality of life score.^[30]^ According to the requirements of the new drug effective standard, after three months of test, the effective standard is a 75% improvement of the PASI score, which is called PASI75.^[29]^ PASI75 combined, with the pruritus score and DQOLS, can evaluate the short-term efficacy of JWLXXF. It needs a certain time to follow up on the recurrence rate and remission period to determine the long-term effect. After 8 weeks of treatment, patients with a pai75 will be followed up and this period will start from the end of the treatment. If there is no recurrence, the follow-up period is 1 year. If there is recurrence, the recurrence of the disease is the end point of the follow-up.

According to the guiding principles for clinical research on new drugs of traditional Chinese medicine (Part III), issued by the Ministry of health in 1997 and the directions of new drugs clinical research (try out) issued by the State Food and Drug Administration in 2002, the recurrence criteria are: new skin lesions appear in the patients who are cured clinically, or the original skin lesions expand, turn red, scale increase, and PASI score increase for ≥1. No recurrence criteria: the same as that at the end of treatment, but with limited skin lesions.^[31]^

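### Section 3.10 gives the chi-square test to all primary outcomes, but most are numeric without cut-points, so their two-arm comparison has no suitable stated test

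*Protocol article*

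**What the plan says.** Section 3.10 (Statistical analysis) of the protocol article states: "The Chi-square test will be used to evaluate the basic baseline characteristics and primary outcomes of the 2 groups". It then names Spearman rank correlation for PASI against the biochemical indexes, and one-way ANOVA with LSD or Tamhane T2 comparisons for the means of multiple samples.

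Section 3.5.1 (Primary outcomes) lists:

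- "PASI: assess the severity of the disease";
- laboratory measures: "the number and distribution of Th1, Th2, Th17, Treg, Th22, and Th9 cells will be determined by ELISA"; expression of four transcription factors by PCR and WB; and "The screening of cytokines, such as IFN-gamma, IL-4, IL-17A, IL-17F, IL-22, TGF-beta, IL-10 and IL-9 will be performed by Bio-Plex suspension chip";
- "Recurrence rate = recurrence cases/follow-up cases", expressed as a percentage;
- "Mitigation period: this remission period - the last remission period".

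Section 3.8 (Sample size calculation) sizes the trial as follows: "To detect a difference of 0.9 SD with 90% power using a 5% significance level", giving 30 per arm, raised to 36 for 20% dropout.

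**The concern.** A chi-square test compares frequencies across categories. To use it on a score, a concentration or a duration, the values must first be grouped, and section 3.5.1 defines no groups for any numeric outcome. Anyone following 3.10 literally must therefore invent cut-points or depart from the plan.

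Two things are at stake. Cut-points chosen once data are in hand leave room for selective results on primary outcomes. Cutting a numeric outcome in two also discards information, so power falls below what section 3.8 intends. A standardised difference of 0.9 SD implies a comparison of means, which is not the test that 3.10 names.

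**Working it through.** **1. Outcome scale against stated test.**

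| Primary outcome (3.5.1) | Scale as defined | Does chi-square fit? |
|---|---|---|
| PASI | numeric severity score, no responder cut-off | only if PASI75 is meant |
| Six T-cell subsets | numeric | no |
| Four transcription factors | numeric expression | no |
| Eight named cytokines | numeric | no |
| Recurrence rate | yes/no per patient | yes |
| Remission-period difference | difference of two durations | no |

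As written, that is 1 + 6 + 4 + 8 + 1 = 20 numeric measures and one proportion.

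**2. Do the other methods in 3.10 fill the gap?** Spearman correlation relates PASI to the laboratory indexes; it does not compare arms. ANOVA is stated for multiple samples, with pairwise follow-up tests that matter only for three or more groups. That suits patients, healthy volunteers and recovered patients. The comparison of the two groups is given expressly to chi-square.

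**3. The plan's own sample size.** Inputs from 3.8: 0.9 SD, 90% power, 5% level (two-sided assumed).

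- Normal formula: n = 2(1.960 + 1.282)² / 0.9² = 2 × 10.51 / 0.81 = 25.9, so 26 per arm. The exact t-test gives 27.
- The plan's 30 is not reproduced exactly, but it errs on the safe side for a comparison of means.
- 36 is 30 × 1.2. Losing 20% of 36 leaves 36 × 0.8 = 28.8, rounded down to 28. Results below use both 28 and 30 per arm.

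**4. Power for a true 0.9 SD difference.**

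- *t-test.* The noncentrality is 0.9 × √(n/2), which is 3.37 at n = 28 and 3.49 at n = 30. Power is 91.1% and 92.9%.
- *Chi-square after a cut.* Assume normal data with a cut c SD above the lower mean. The proportions above the cut are 1 − Φ(c) and 1 − Φ(c − 0.9). Exact power is the total binomial probability of all result pairs whose uncorrected Pearson statistic exceeds 3.84.

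| Cut c | Proportions | Power, 28 per arm | Power, 30 per arm |
|---|---|---|---|
| 0.45 (midway, best tried) | 32.6% vs 67.4% | 74% | 79% |
| 1.5 | 6.7% vs 27.4% | 57% | 60% |
| 2.0 | 2.3% vs 13.6% | 34% | 38% |

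No cut tried reaches 90% at either size. By the usual two-proportion formula, the midway cut would need 42 per arm for 90% power, and the 6.7% vs 27.4% cut 67.

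**5. Remission period.** Section 4.2 (Clinical efficacy evaluation basis) says: "If there is no recurrence, the follow-up period is 1 year". The current remission is therefore censored at 1 year in patients without recurrence, and for them the difference from the previous remission is not fully observed. Neither chi-square nor a plain comparison of means handles that.

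**The case against.** The strongest defence is that both stated objectives have a suitable method. The abstract names the effect on relapse rate, which chi-square suits, and the correlation of PASI with cytokines and cell numbers, which Spearman suits. PASI75 is also the gate to follow-up and the efficacy standard in section 4.2, so chi-square on PASI75 is a plausible intention. This stands in part: the gap is confined to the two-arm comparison of the numeric outcomes, and for PASI the text is ambiguous. It does not remove the gap, because 3.5.1 defines PASI as severity, and no PASI75 reading reaches the laboratory measures or the remission difference.

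Some stronger readings go beyond the documents:

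- *That the plan makes an invalid test inevitable.* A chi-square test on pre-specified categories is valid; what it loses is power. The fault is that no categories are specified.
- *That a definite power claim for PASI is broken.* Section 3.8 says that the primary outcome was unknown and uses a generic effect size in a pilot trial. The power figures illustrate the mismatch and describe no named endpoint.
- *That the power loss lies in a narrow band.* It depends strongly on the cut, and there is no floor near the best value.
- *That leaving out baseline adjustment is itself an error.* An unadjusted comparison of randomised arms is valid, and covariates are commonly left to an analysis plan.
- *That every laboratory measure can be adjusted for baseline.* The initial assessment in section 2 lists routine tests and not cytokines or T-cell subsets, and Table 1 is not shown.

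Nor can the point be dismissed as detail left to an analysis plan, since the article states a test and applies it to all primary outcomes.

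**Conclusion.** The point holds in this form: for the two-arm comparison of the PASI score, laboratory measures and remission-period difference, section 3.10 states a test that does not fit their scale, and no other sentence clearly supplies one. Chi-square is appropriate for recurrence yes/no, and for PASI75 if that is intended.

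If a numeric outcome were cut in two to make chi-square usable, power for a 0.9 SD difference would fall from about 91% to at most about 74% among the cuts tried with 28 per arm, or from 93% to 79% with 30. Off-centre cuts do much worse. These figures assume normal data, two-sided 5% testing and an uncorrected chi-square. They do not describe recurrence or remission, which are observed only in patients who enter follow-up. The scale mismatch itself depends on none of these assumptions.

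**What to change.** Reword section 3.10 so that each primary outcome has a test that suits its scale:

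- **Recurrence yes/no, and PASI75 if used:** chi-square or Fisher's exact test. State whether the PASI outcome is the score or PASI75.
- **PASI score:** ANCOVA with treatment and the baseline PASI already collected, or a mixed model over the scheduled visits at weeks 2, 4, 6 and 8. Section 3.5.1 fixes no time point, so name one.
- **Laboratory measures:** a two-sample or rank test on suitably transformed values, adjusting for baseline only where a baseline sample exists. Keep ANOVA for comparisons that include the healthy and recovered groups, and say so.
- **Remission:** analyse time from end of treatment to recurrence by a time-to-event method, censored at 1 year, with the previous remission duration as a covariate. This replaces the simple difference in 3.5.1, so that definition must change too.

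The cost is a small wording change to 3.10 and to the remission outcome in 3.5.1. Baseline adjustment of laboratory measures should not be promised until the baseline sampling is confirmed.

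### Chi-square is assigned to the primary outcomes of the two arms, but most of those outcomes are quantities and the trial is sized on a difference in means

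*Protocol article*

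**What the plan says.** Section 3.10 (Statistical analysis) ties one test to the primary outcomes in the two arms: "The Chi-square test will be used to evaluate the basic baseline characteristics and primary outcomes of the 2 groups". It names two other analyses that could touch the same data. One is a correlation: "The Spearman rank correlation analysis of the correlation between PASI and biochemical indexes, will be used". The other is "The one way ANOVA test will be used to compare the mean of multiple samples", with LSD or Tamhane T2 as follow-up depending on whether variances are equal. Neither the outcomes nor the groups for the ANOVA are given.

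Section 3.5.1 (Primary outcomes) lists PASI, the laboratory assessments, the recurrence rate, and this remission period minus the last one. The laboratory part has three blocks:
- Cells: "the number and distribution of Th1, Th2, Th17, Treg, Th22, and Th9 cells will be determined by ELISA".
- Transcription factors: "The expression of the transcription factors T-bet, GATA3, ROR gamma t, Foxp3 gene will be investigated by PCR and WB".
- Cytokines: "The screening of cytokines, such as IFN-gamma, IL-4, IL-17A, IL-17F, IL-22, TGF-beta, IL-10 and IL-9 will be performed by Bio-Plex suspension chip".

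Section 3.8 (Sample size calculation) says: "To detect a difference of 0.9 SD with 90% power using a 5% significance level, a sample size of 30 per arm would be required". It then raises this to 36 per arm for 20% dropout.

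**The concern.** Chi-square compares counts in categories. A cytokine concentration, an expression level, a cell count or a length of time has no categories until someone chooses a cut, and the article gives none. The test assigned to the primary outcomes therefore does not fit most of them.

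Two things are at stake. First, cutting a measurement into two classes discards information, and the cost depends on where the cut falls; with no cut fixed in advance, the result would also depend on that choice. Second, the sample size rests on a standardised difference in means. If the analysis is a test of proportions, the stated 90% power does not describe it.

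**Working it through.** **1. Match the test to the outcomes (sections 3.5.1 and 3.10).**

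| Primary outcome | Type | Does chi-square fit as measured? |
|---|---|---|
| Recurrence rate | yes/no | yes |
| PASI as a PASI75 response | yes/no | yes |
| PASI as a score | quantity | no |
| 6 T-cell subsets | quantity | no |
| 4 transcription factors | quantity | no |
| 8 named cytokines | quantity | no |
| Remission-period difference | quantity | no |

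Markers: 6 + 4 + 8 = 18. This is a minimum, because the cytokines are given as examples, cells are described by both number and distribution, and each factor is measured by two assays.

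**2. Reproduce the plan's sample size.** Inputs from section 3.8: d = 0.9 SD, power 90%, alpha 5% (two-sided assumed).

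n per arm = 2(1.960 + 1.282)² / 0.9² = 25.9, so 26; the exact t-test needs 27. The stated 30 is not reproduced but errs on the safe side. For dropout, 30 × 1.2 = 36, which is the plan's figure; 30/(1 − 0.2) would be 38. Neither difference affects this point.

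**3. Power at 30 per arm with the measurement kept continuous.** Noncentrality = 0.9/√(2/30) = 3.486, with 58 df. Exact two-sided t-test power is 92.9%.

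**4. Power at 30 per arm after a two-class cut.** Assumed: normal data, equal SD, two classes.

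*Fixed cut midway between the arm means.* The proportions above the cut are Φ(−0.45) = 0.326 and Φ(0.45) = 0.674, a difference of 0.347.
- SE under the null: √(2 × 0.5 × 0.5/30) = 0.129.
- SE under the alternative: √(2 × 0.326 × 0.674/30) = 0.121.
- Power = Φ[(0.347 − 1.96 × 0.129)/0.121] = 78.2%.
- Simulation gives 79%, or 70% with continuity correction.
- By formula, 90% power needs 42 per arm (48 with correction).

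*Cut at the pooled sample median.* Simulation gives 83%, or 66% with continuity correction.

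*Other fixed cuts, by formula.* Control median 74.4%; control 75th percentile 77.3%; pooled upper quartile 67.7%; control 25th percentile 54.3%.

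**5. How much of the 66% is an artefact?** With a pooled-median split, the gap between the arms' counts above the median moves in steps of 2, and z = (gap/n)/√(0.5/n).
- n = 30: a gap of 8 gives z = 2.07 uncorrected (significant) but 1.81 corrected (not significant), so the correction demands a gap of 10.
- n = 36: a gap of 8 gives z = 1.89 uncorrected (not significant). A gap of 10 gives 2.36, or 2.12 corrected (both significant). The threshold is the same either way, and simulated power is 81% with or without correction.

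The drop from 83% to 66% at 30 per arm therefore partly reflects discreteness.

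**6. If all 36 per arm are analysed.** The t-test has 96.5%. The midway cut has about 84% by simulation (78% with correction). The dropout allowance does not close the gap.

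**7. The ANOVA reading.** Pool over four groups (30, 30, 15, 15), giving 86 df. With equal SDs and no requirement that the overall F-test be significant first, the LSD contrast between the two arms has 93% power at 0.9 SD, the same as the t-test.

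**The case against.** The strongest reply is that the ANOVA sentence was meant for the laboratory data. The trial has four groups: two arms, 15 healthy volunteers and 15 recovered patients. The marker means are the natural thing to compare across them, and LSD or Tamhane T2 would include the contrast between the arms with no loss of power. This reading is plausible, so a reader who infers that the plan contains no valid between-arm test of the markers goes too far. What remains is that the ANOVA is tied to no outcome or group, while the primary outcomes of the two arms are expressly given to chi-square. If ANOVA was intended, the chi-square sentence is wrong and needs the same correction.

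Other limits also stand:
- The article plans no dichotomisation. A reader might infer that cut-points will be chosen after seeing the data, but nothing says so. The power figures show what the sentence would cost if followed literally.
- The 0.9 SD is a generic effect size, chosen because the primary outcome was unknown. It is not an estimate for any marker.
- A comparison that ignores pre-treatment values is valid in a randomised trial. Adjustment gains precision and is not needed for validity.
- The objectives in the abstract are the relapse rate and the correlation of PASI with the markers. Chi-square and Spearman suit those. The markers are nevertheless listed as primary, and a correlation does not compare the arms.
- An article may leave model details to a fuller document. That does not answer this point, because the article names a test and the test does not suit the outcomes it is given.

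**Conclusion.** The point holds as a mismatch between the named test, the outcomes and the sample-size basis. Chi-square fits recurrence and a PASI75 analysis. It does not fit at least 18 markers, the remission-period difference, or PASI as a score.

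Taken literally at 30 per arm and 0.9 SD, the test would lower power from 93% to about 79 to 83%, or about 66 to 70% with continuity correction, and further with a less central cut. These figures assume normal data, equal SDs, two classes and a two-sided 5% level, and the corrected median-split figure is partly discreteness. They illustrate the cost and do not predict what the trial will do.

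The correction should be made, since the markers are declared primary and the wording decides how they are tested. The recurrence comparison does not suffer from this mismatch.

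**What to change.** Rewrite the test assignment in section 3.10 so that each primary outcome has a test that suits it:
- Restrict chi-square to the categorical outcomes: recurrence and PASI75 response.
- Compare the two randomised arms on each quantitative primary outcome on its continuous scale, and report the difference or ratio with a 95% CI.
- Where a pre-treatment value is collected, use ANCOVA with that value as covariate, on the log scale for markers. PASI is assessed at the first visit. The baseline list in section 2 does not mention the markers and Table 1 is not shown, so whether they are sampled before treatment has to be confirmed.
- Where there is no pre-treatment value, use an unadjusted two-group comparison of means or ranks.
- State which outcomes and groups the one-way ANOVA covers.

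The cost is a few sentences of wording and a little more analysis work. It needs no extra patients and no extra visits.
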